### Recruitment

The patients are identified in the lung cancer pathway at the time of referral to the oncology service, in the MDT meetings or in an oncology clinic. They are screened at the outpatient clinic appointment and offered the Participant Information Sheet (PIS) (online supplemental appendix 5). They are consented at the time of booking the radiotherapy or at the subsequent clinic appointment or the planning CT appointment using the consent form as shown in online supplemental appendix 6. A study flow diagram is shown in figure 2. Information is collected regarding participants who are screened and for participants who are not recruited into the study, or those who decline the study, where data are being collated for Consolidated Standards of Reporting Trials or other similar reasons for reporting the generalisability of the results.

**Figure 2 F2:**
[figure not shown]
Flow of participants through the study. ECOG PS, Eastern Cooperative Oncology Group Performance Status; QoL, quality of life; RT, radiotherapy.

Once entered into the study, the schedule of follow-up events does vary according to the further treatment plan for the patients. This is highlighted in figure 3.

**Figure 3 F3:**
[figure not shown]
(A) Schedule of events—for patients who have no treatment planned after radiotherapy. (B) Schedule of events—for patients who will have chemotherapy after radiotherapy. (C) Schedule of events—for patients who will have oral systemic therapy after radiotherapy. (D) Schedule of events—for patients who will have immunotherapy after radiotherapy. X* - Standard of Care. The yellow highlighted boxes are procedures that are outside of the standard of care. The times at which the participant is followed-up depending on whether or not the participant has further treatment post-radiotherapy. These are not exact timepoints but a guideline for procedures. Visits 1-3 must be completed within +/- 3 days and from visits 4-9 must be completed within +/- 1 week. CXR (Chest X-ray) ; ECOG PS (Eastern Cooperative Oncology Group Performance Status); FBC, (full blood count); F/U (follow-up); GFR (glomerular filtration rate); LFT (liver function tests); QoL (quality of life); RT (radiotherapy); SOE (schedule of events); U&E (urea and electrolytes); YOB (year of birth).

### Data collection

The source documentation includes electronic hospital records and treatment databases, including radiotherapy planning and treatment databases. The necessary data are collected and transcribed onto a case report form (CRF). It is an electronic document (eCRF). The CRF data are used to perform the statistical analysis for the study. As this is a multicentre study, we are carrying out direct electronic entry and automatic upload into the database, for speed efficiency and accuracy.

The data are collected by co-investigators and other authorised personnel listed in the delegation log.The types of data that are collected include patient demographics, tumour characteristics, details of treatment including radiotherapy dose-volume parameters, toxicity data and follow-up data.

### Data management

On confirmation of eligibility, participants are assigned a unique ID number, which is used to identify all documents associated with that participant for the duration of the study. All data, including source documents and eCRFs, is stored exclusively on hospital computer systems that are password-protected and access to these is defined and controlled by those on the delegation log. Direct access is granted to authorised representatives from the Sponsor, host institution and the regulatory authorities to permit study-related monitoring, audits and inspections—in line with participant consent. Following the resolution of queries and confirmation of study close-out by the chief investigator, all essential documentation will be transferred to a third-party archiving service, which provides suitable fire and water-resistant facilities. Study files will be archived for a period of 10 years. Access to the study documentation is restricted to named individuals within the study team with express permission from the chief investigator.

### Statistical methods

All 37 patients who consented to and were recruited to the study will be included in the study flow diagram and the baseline characteristics tables. Descriptive statistics will be used to summarise the distribution of variables. Continuous variables will be reported with means and 95% CIs, if normally distributed, or medians and IQRs otherwise. Categorical variables will be reported using frequencies and percentages.

As the feasibility of the protocolised treatment regimen is core to the study design, a detailed investigation into the adherence of patients to the protocolised study treatment will be undertaken, including variation around the individual fractions’ dose and timing, as well as the received total dose and overall duration of each patient’s treatment course.

The analysis population for study endpoint assessment will include the set of patients who start treatment and provide information on treatment completion and any oesophagitis incidents, and their severity, occurring during their RT and for 4 weeks after completion. The primary outcome will be reported using a frequency, percentage and associated 95% CIs, and compared against the previously specified cut-off points for the stage 1 and stage 2 analyses. Weekly toxicity profiles will be reported using frequencies and percentages. To assess treatment efficacy, TTP from completion of RT will be graphically reported using a Kaplan-Meier plot, and rates and medians, with associated CIs, will be reported. PROMS on quality of life will be scored using appropriate manuals. No statistical testing will be performed. A detailed statistical analysis plan was drafted by the study statistician and approved by the chief investigator and an independent statistician prior to all data analysis timepoints.

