**Trial registration number:**

NCT06483308.

Strengths and limitations of this studyInclusion and exclusion criteria were peer reviewed by patient and public involvement groups and the National Cancer Research Institute (NCRI) lung-Clinical Studies Group and tightened to make them relevant to the real-world patient population, allowing for rigorous hypothesis testing in a representative sample population.The primary endpoint is valid, reproducible, relevant to the target population and responsive to the intervention being studied.Simons’s two-stage design is a simple, ethical and efficient adaptive design, with planned interim analysis and clear criteria for stopping or progressing to the next stage; this design is best suited to our phase II oncology trial, where the primary endpoint for each participant is obtained within 4 weeks of their completing radiotherapy.The patient population is prone to high rates of patient loss or attrition from disease progression or death; therefore, our sample size allows for a 15% drop-out rate.

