### Outcomes

#### Primary outcome

The proportion of patients successfully completing treatment without reporting grade 3–4 oesophagitis, within 4 weeks of completing RT (using CTCAE version 4.03), out of all patients starting treatment in this study. The time points at which the toxicity will be assessed and recorded within 12 months of completion of radiotherapy are described in the schedule of events.

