### Sample size

The primary endpoint is the proportion of patients successfully completing treatment without reporting grade 3–4 oesophagitis, using CTCAE version 4.03 out of all patients starting treatment within this study.

The study regimen will be considered as:

Feasible, if >70% patients complete treatment and do NOT report grade 3–4 oesophagitis.Not feasible, if <45% patients complete treatment and do NOT report grade 3–4 oesophagitis.

Simon’s two-stage design (Simon, 1989) ^26^ has been adopted. The null hypothesis that the true response rate is 45% will be tested against a one-sided alternative. Recruiting 37 patients will allow detection of the rate being ≤45% or ≥70%, with one-sided 5% significance and 85% power. This calculated sample size allows for a 15% attrition rate.

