#### Stage 1 analysis

Patients will be accrued until 11 patients have primary endpoint information available. If there are five or fewer patients who completed treatment and did NOT report grade 3–4 oesophagitis (ie, six or more who either failed to complete treatment, or reported grade 3–4 oesophagitis), the study will be stopped early for futility. Otherwise, it will continue to recruit.

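### The primary endpoint has two conflicting denominators: all patients who start treatment, or only starters with full completion and 4-week oesophagitis information

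*Protocol article*

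**What the plan says.** All references are to the protocol article.

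- **Primary outcome** and **Sample size** give the endpoint as the proportion completing radiotherapy without grade 3–4 oesophagitis, "out of all patients starting treatment in this study" (Sample size repeats this almost word for word).
- **Statistical methods** defines the population for endpoint assessment as "the set of patients who start treatment and provide information on treatment completion and any oesophagitis incidents", with the oesophagitis information running through radiotherapy and for 4 weeks afterwards.
- **Stage 1 analysis**, **Stage 2 analysis** and **Interim analysis** count patients who have primary endpoint information: 11 at stage 1 and at least 31 at stage 2. The study stops at 5 or fewer successes of 11, and the null is rejected at 19 or more successes.
- **Stage 1 analysis** and **Interim analysis** treat non-completion as failure. The stopping condition is restated as "six or more who either failed to complete treatment" or had the toxicity.
- **Sample size** states "This calculated sample size allows for a 15% attrition rate". The strengths and limitations box describes these patients as "prone to high rates of patient loss or attrition from disease progression or death; therefore, our sample size allows for a 15% drop-out rate".
- **Trial status** reports 23 patients recruited and a stage 1 decision to continue.

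**The concern.** A treated patient without full information is in the denominator under Primary outcome and out of it under Statistical methods. Two groups are affected.

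- **Non-completers.** The stage 1 rule makes them failures. Statistical methods asks for completion information and 4-week oesophagitis information jointly. Taken at its word, it can drop a patient who stopped or died during radiotherapy and has no later toxicity record.
- **Completers who die or are lost before week 4.** They belong to the all-starters denominator and not to the analysis set. The outcome definition does not clearly say whether they are failures.

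The article itself attributes the expected loss to progression or death, so exclusion is unlikely to be unrelated to outcome in a trial of safety and completion. At stake is the single go/no-go test: a few patients, counted or not, could decide it, and the choice could be made after their outcomes are known.

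**Working it through.** **Inputs from the article.** Null rate 45%, target rate 70%, one-sided 5% significance, 85% power, 15% attrition, 37 recruited (Sample size). Stage rules 11 and 31 patients, continue at 6 or more successes, reject at 19 or more (Stage 1 and Stage 2 analysis). Background 30-day mortality of 9% and about 14% (Introduction), used only as reference points for the size of early loss.

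**Step 1: reproduce the design.** With n₁ = 11 and n = 31, the exact rejection probability at rate p is

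P(p) = Σ (x = 6 to 11) Bin(x; 11, p) × Pr[Bin(20, p) ≥ 19 − x].

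This gives P(0.45) = 0.0439 and P(0.70) = 0.8505. For recruitment, 31/0.85 = 36.5, rounded up to 37. The article's figures are correct, and only the denominator is at issue.

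**Step 2: how many starters can be excluded.** 37 − 31 = 6. The allowance runs from recruited to evaluable patients, so some of the six may never start radiotherapy. Excluded starters therefore range from 0 to about 6 of 37.

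**Step 3: worst case.** Assume that the all-starters rate is 45%, a share m of starters is excluded, and every excluded starter is a non-success. The rate in the analysed set is then q = 0.45/(1 − m).

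| m | q | Chance of declaring feasibility, P(q) |
|---|---|---|
| 0 | 0.450 | 4.4% |
| 2% | 0.459 | 5.4% |
| 5% | 0.474 | 7.4% |
| 9% | 0.495 | 11.2% |
| 14% | 0.523 | 18.3% |
| 15% | 0.529 | 20.1% |

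**Step 4: relax the worst case.** If only a fraction f of the excluded are non-successes, q = [0.45 − m(1 − f)]/(1 − m).

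- f = 0.75: 6.8% at m = 9%, 8.9% at m = 14%, 9.4% at m = 15%.
- f = 0.55: q = 0.45 for every m, so the error rate stays at 4.4%. This is the break-even point, because 1 − 0.45 = 0.55.
- f = 0.50: 3.9% at m = 9%, 3.6% at m = 15%. There is no inflation.

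**Step 5: the same observed result under each denominator.** 19/31 = 61.3%. If all 37 started and the six without information are non-successes, 19/37 = 51.4%.

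**Step 6: cut-offs with all starters analysed, stage 1 rule unchanged.**

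| Starters analysed | Reject at | Alpha | Power at 70% |
|---|---|---|---|
| 31 | ≥ 19 | 0.044 | 0.851 |
| 37 | ≥ 22 | 0.045 | 0.883 |
| 37 | ≥ 19 | 0.175 | 0.920 |

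**Step 7: cost in power.** If 70% is the rate among evaluable patients only, and all those lacking information count as non-successes, the all-starters rate is 0.70(1 − m). Power of the 31-patient rule is then 0.74 at m = 5% (rate 0.665), 0.63 at m = 9% (0.637) and 0.45 at m = 15% (0.595).

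**The case against.** A reader might infer that deaths and early drop-outs are systematically removed when they should count as failures, so that the reported rate must be too favourable. The article does not support that reading, for four reasons.

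- **Non-completers are already failures under the stage rules.** Their completion status is obtainable from treatment records, and a 4-week period after completion has no meaning for someone who did not complete. Reading the sections together, these patients probably stay in. This stands as the likelier reading, but the joint requirement in Statistical methods still permits the other one.
- **A completer who dies in week 3 without severe oesophagitis is not a failure by the wording of Primary outcome.** That patient could even be a success, in which case exclusion would lower the observed rate. This stands: the direction of the bias is not fixed by the text.
- **Partial information may be usable.** Toxicity is reported weekly, and the article does not say that records up to death are discarded.
- **The share excluded may be small.** Eligibility rules out patients with a likely life expectancy under 6 months, so mortality of 9% to 14% in unselected series may not carry over. The 15% allowance may also include patients who never start.

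The fine detail of missing-data handling could sit in the statistical analysis plan, which is not shown. That does not answer the point, because the article states both populations itself and they differ.

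**Conclusion.** The point holds as a conflict in the primary denominator, not as a demonstrated favourable bias. The same treated patient can be in or out depending on the section applied, and the loss is expected to be related to outcome.

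The worst-case false-positive figures (5.4% at 2% excluded, rising to 20.1% at 15%, against 4.4% planned) are upper bounds. They assume that every excluded starter is a non-success and that the all-starters rate is exactly 45%. With three quarters non-successes, the error rate is still above 5% at exclusions of 9% or more. With 55% or fewer there is no inflation. The article does not allow a choice among these cases, which is why the counting rule has to be written down before the final data are seen.

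**What to change.** Make these changes before the stage 2 analysis.

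1. In Statistical methods, define the primary analysis set as every patient who starts radiotherapy, in line with Primary outcome and Sample size.
2. State that non-completers count as failures whatever their follow-up.
3. State that completers who die or have missing status before week 4 count as non-successes. This is a conservative analysis rule that the current outcome wording does not contain, so it should be recorded as a clarification of the endpoint.
4. Report the complete-information set as a sensitivity analysis.
5. Tie the cut-off to the number analysed: at least 19 of the first 31 starters (alpha 0.044), or at least 22 if 37 starters are analysed (alpha 0.045, power 0.883). Applying 19 to 37 starters would give alpha 0.175.
6. Because stage 1 has already been analysed, record whether its 11 patients were the first 11 starters. The error rates above assume that they were.

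**Cost.** The change is one of wording and a short amendment. The observed rate may be less favourable. If the 70% target was meant for evaluable patients only, power of the 31-patient rule falls from 0.85 to 0.74, 0.63 or 0.45 when 5%, 9% or 15% of starters lack information.

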Clinically relevant organs at risk for palliative thoracic RT are the oesophagus, normal lung tissue and spinal cord. Within the Cochrane review (2015), radiation-related oesophagitis was reported in 8 out of 14 studies (1301 patients) either as patient-reported or physician-assessed toxicity.^17^ The mean rate of grade 3–4 oesophagitis was reported as 25.7% in the intervention groups (that used more fractions) and 22.3% within the control groups (using fewer fractions). Radiation pneumonitis was graded or reported in only 3 out of 14 trials (533 patients) included in the meta-analysis, with the mean reporting rate of 3.9% in the control groups and 2.4% in the intervention group.^17^ The spinal cord remains an organ of concern because of the rare but serious late complication of radiation myelopathy (RM), that was reported by the Medical Research Council Lung Cancer Working Party (MRC-LCWP) in 1996.^18^ The pooled data on 1048 patients from three RCTs conducted by the MRC-LCWP was analysed, and RM was reported in five patients treated with either 17 Gy in 2 fractions (1 week apart) or 39 Gy in 13 fractions (5 fractions/week).^19^ The median survival after palliative RT ranges from 6.2 to 9 months^20^ and 1-year survival was reported as 39%.^17 18^ More recently, 30-day mortality rates have been reported as 9% in a large retrospective single-centre study and about 14% in a large population-based study.^20 21^

The aim of the present study is to investigate the safety and feasibility of reducing the number of rt fractions and the treatment duration, compared with the current standard of care (36 Gy in 12 fractions over 16 days), by using 30 Gy in 6 fractions over 12 days (figure 1), provided the well-defined dose and biologically effective dose (BED) constraints are achievable.

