## Methods and analysis

The proposed regimen of 30 Gy in 6 alternate-day fractions is comparable to the current standard treatment for tumour control, with similar BED and equivalent dose in 2 Gy fractions.^22^,^25^ From established models for effects of radiation, the proposed regimen should have similar efficacy for tumour control, although this needs to be tested in a phase III RCT, once the regimen is shown to be safe and feasible.^22^,^24^ High-dose palliative RT should be short and sharp and enable appropriate patients to move promptly onto definitive systemic therapy. A 12-fraction, 16-day radiotherapy regimen seems inappropriate when 9%–14% of patients die within 30 days and survival is limited.^20^ With advances in RT planning, verification and delivery techniques, it may be possible to safely treat patients with an adequate dose of palliative RT in fewer fractions, as demonstrated in a recent planning study.^25^ It is possible to keep doses to normal tissues and organs within tolerance by carefully adhering to the established dose constraints during planning and robust verification before delivery.

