#### Secondary outcomes

Toxicity assessments for common acute and late toxicity using CTCAE version 4.03.Assess the feasibility of recruiting patients (number of patients screened, eligible, recruited and withdrawn) and treating them in a timely manner while maintaining necessary gaps and washout periods. Record the time at which systemic therapy was initiated from recruitment and from the end of radiotherapy.TTP—documentation of the time at which disease progression occurs from the end of radiotherapy.PROMS responses using EORTC QLQ-C30 and QLQ-LC13 at baseline and timepoints as described in the schedule of events.Calculations of cost savings from the proposed treatment regimen.The acceptability of the treatment to participants by recording how many participants participate in the study versus how many consent versus how many complete treatment.

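### Time to progression counts progression alone and runs from completion of RT, so its Kaplan-Meier rates would overstate the probability of progression and the origin is unclear for non-completers

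*Protocol article*

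**What the plan says.** The Statistical methods section of the protocol article gives TTP its purpose and its origin, "To assess treatment efficacy, TTP from completion of RT", and then its estimator: "TTP from completion of RT will be graphically reported using a Kaplan-Meier plot, and rates and medians, with associated CIs, will be reported". The Secondary outcomes section defines the measure as "documentation of the time at which disease progression occurs from the end of radiotherapy". Neither section mentions death. No progression-free or overall survival outcome is listed, so TTP is the only summary that the article labels as efficacy.

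On who is analysed, Statistical methods says: "The analysis population for study endpoint assessment will include the set of patients who start treatment and provide information on treatment completion". Non-completers are expected. The Stage 1 analysis section counts as failures "six or more who either failed to complete treatment, or reported grade 3–4 oesophagitis".

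On mortality, the Introduction reports that "The median survival after palliative RT ranges from 6.2 to 9 months", with 39% alive at 1 year, and that "30-day mortality rates have been reported as 9% in a large retrospective single-centre study and about 14% in a large population-based study". The strengths and limitations box describes a population prone to loss through progression or death. Trial participation ends at the 12-month visit.

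**The concern.** Two features of the stated summary do not fit this population.

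- **Death.** If progression is the only event, a patient who dies first can enter a Kaplan-Meier analysis only as censored. The estimator then treats that patient as still able to progress later. One minus the curve describes progression in a hypothetical setting where nobody dies first, and not the share of patients who progress. A reader may also take the median for time alive without progression, which it is not.
- **Origin.** Completion of RT is a date that non-completers do not have, yet the endpoint population is defined by starting treatment. If they are dropped, the curve is conditional on finishing the course. If they are kept, the origin has to be something other than completion.

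At stake is how the one efficacy summary reads when the case for a phase III trial is made. The feasibility decision is not at stake.

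**Working it through.** **The plan's own figures.** The article gives no size, event count or expected rate for TTP, so there is no TTP figure to reproduce. The primary design does reproduce. Continuing with 6 or more successes of 11 and rejecting with 19 or more of 31 gives exact one-sided alpha 0.0439 and power 0.8505 for 45% against 70%. Allowing for 15% attrition, 31/(1 − 0.15) = 36.5, rounded up to 37. Nothing below affects this.

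**Inputs for the illustration.**

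- Follow-up of 12 months (Ancillary and post-trial care).
- Cause-specific median TTP of 6 months. This is assumed. It gives λp = ln 2/6 = 0.1155 per month.
- Hazard of death without progression λd = 0.02, 0.04 or 0.06 per month. This is assumed. For scale, 39% alive at 1 year implies an all-cause hazard of −ln(0.39)/12 = 0.078 per month, so each value lies below the total.
- Both hazards are constant, and death is independent of progression.

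**Formulas.**

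- Kaplan-Meier with deaths censored: 1 − exp(−12 λp) = 1 − exp(−1.386) = 75.0%, whatever λd is.
- Cumulative incidence of progression: λp/(λp + λd) × [1 − exp(−12(λp + λd))].
- Median time to progression or death: ln 2/(λp + λd).

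| λd per month | 1 − KM at 12 months | Cumulative incidence | Gap (points) | Median, progression or death (months) |
|---|---|---|---|---|
| 0.02 | 75.0% | 0.852 × 0.803 = 68.5% | 6.5 | 0.693/0.1355 = 5.1 |
| 0.04 | 75.0% | 0.743 × 0.845 = 62.8% | 12.2 | 0.693/0.1555 = 4.5 |
| 0.06 | 75.0% | 0.658 × 0.878 = 57.8% | 17.2 | 0.693/0.1755 = 3.9 |

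The Kaplan-Meier median for TTP is 6.0 months in every row.

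**Wider range.** Take median TTP as 4, 6 or 9 months, and let death without progression be 25% to 50% of the hazard implied by median survival of 6.2 to 9 months. The 12-month gap then runs from 5.5 points (60.3% against 54.8%) to 16.7 points (87.5% against 70.8%).

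**Origin.** The two descriptions, side by side:

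- Statistical methods: completion of RT. A patient who stops early or dies during the course has no such date.
- Secondary outcomes: end of radiotherapy. This can be read as the last fraction given, which exists for everyone who starts.

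The descriptions coincide for completers and may diverge for non-completers.

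**The case against.** The strongest reply is that the article never says that deaths are censored. Event and censoring rules commonly sit in the full protocol or the SAP, and Statistical methods says that a detailed SAP was written and approved. That stands to this extent: bias is the consequence of following the article as written, and not an established fact about the final analysis. It does not dispose of the point, because the article already names the event, the origin and the estimator. An SAP using cumulative incidence or progression-free survival would depart from it.

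Two stronger readings are tempting and should not be drawn.

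- A reader might infer that this trial faces 30-day mortality of 9% to 14%. The article does use the range in its rationale ("9%–14% of patients die within 30 days and survival is limited"), and on 31 patients it would mean 0.09 × 31 = 2.8 to 0.14 × 31 = 4.3 early deaths. But the rates are all-cause and come from external cohorts, whereas the trial excludes patients expected to live less than about 6 months. The competing event is death without prior progression, for which no figure is given.
- A reader might infer that non-completers have no start date at all. The Secondary outcomes wording allows the last fraction given, so the defect is an unclear origin.

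Other replies also carry weight. TTP with deaths censored is a recognised cause-specific summary, and a TTP median longer than a progression-free survival median partly reflects a different quantity. The planned course is 12 days, so moving the origin to the first fraction shifts times by about 0.4 month (12/30.4) for patients treated on schedule. With 31 patients the 95% half-width around 75% is about 1.96 × √(0.75 × 0.25/31) = 15 points before any censoring, so the smaller gaps lie within sampling error. The larger gaps rest on a high assumed share: 0.06 is about three quarters of 0.078. Finally, no statistical testing is planned and efficacy is left to a phase III trial.

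**Conclusion.** The point holds as a modest one. Progression-only events analysed by Kaplan-Meier would yield 12-month rates above the true proportion progressing: 75% against 58% to 69% in the main illustration, and 5.5 to 16.7 points too high over the wider range. These sizes depend on assumed constant, independent hazards and on an assumed TTP median and rate of death without progression. None of these comes from the trial. The direction follows from the method whenever some patients die without progression and are censored. Read instead as progression-free survival, the same curve would look too favourable.

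The two descriptions of the time origin need to be reconciled, because only one of them can be applied to every patient who starts RT. The documents do not support saying that the efficacy summary is already biased. The outcome is secondary and descriptive, and the Simon boundaries are unaffected. It is worth considering, and it is not a condition for the trial's main conclusion.

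**What to change.** - Use one time origin, worded identically in Secondary outcomes and Statistical methods, that exists for every patient who starts RT. The date of the first fraction is one such choice.
- Report progression as an Aalen-Johansen cumulative incidence with death without progression as a competing event, with confidence intervals at the chosen times.
- Report progression-free survival (progression or death from any cause) by Kaplan-Meier beside it, with its median and confidence interval.
- If the SAP already handles death this way, align the protocol wording with it.

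The cost is a little more analysis and a shorter headline median: about 3.9 to 5.1 months in place of 6.0 under the assumptions above. The Data collection section mentions follow-up data without naming the date of death, so the team should confirm that it is captured. Trial status reports 23 of 37 patients recruited, so the change can be made before the final analysis.
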